### Sample Size

The sample size for this study was calculated using G*Power (version 3.1.9.2; Heinrich Heine University Düsseldorf) and Microsoft Excel, applying the paired sample formula. Data from the study by Bailey et al [47,48] reported pre- and postintervention knowledge scores with mean values of 16.88 (95% CI 16.17-17.19) and 20.88 (95% CI 20.36-21.41), respectively. To convert the CI into SD, statistical calculations were performed using the standard normal distribution and t-distribution, yielding SD values of approximately 2.2 for preintervention and 1.2 for postintervention scores. With a significance level (α) of .05, power (1–β) of 80%, an estimated effect size of 1.2, and a correlation coefficient of 0.5, the required sample size was determined to be 223 participants. Accounting for a 20% dropout rate [49], the final sample size was adjusted to 267 school-going adolescents to ensure sufficient statistical power for detecting meaningful differences in knowledge scores.

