**Methods:**

The investigation will assess the efficacy of the RAAHI intervention among 267 adolescents across 4 private schools in GB using an interrupted time-series design with a pre-post test framework. The first intervention, RAAHI, a suicide literacy module, is designed to empower participants with the knowledge and skills to recognize signs of suicidal ideation, engage them empathetically, and connect individuals in crisis with appropriate support. The second intervention, safeTALK, a 4-hour educational workshop, incorporates presentations, videos, discussions, and interactive sessions to teach participants the tell, ask, listen, and keep safe steps. Outcome measures include changes in knowledge, confidence, willingness to intervene, and help-seeking behaviors, analyzed using descriptive statistics, 2-tailed paired *t* tests, and ANOVA. Ethics approval was granted by the Aga Khan University Ethics Review Committee (2023-8509-24844).

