### Research Questions

The primary research question about suicidal ideation is as follows: What is the effect of suicide prevention programs (RAAHI and safeTALK) in reducing suicidal ideation among school-going adolescents in GB?

The secondary research question is as follows: What is the effect of suicide prevention programs (RAAHI and safeTALK) among school-going adolescents in GB on (1) perceived suicidal awareness; (2) perceived Social Support Questionnaire; (3) suicide literacy; (4) attitude toward seeking help related to suicidal ideation; (5) life attitude schedule; (6) depression, anxiety, and stress level; (7) adaptive coping strategies; and (8) self-efficacy.

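### The sample-size inputs give 5 to 22 pairs rather than 223, the dropout step is miscalculated, and no power is stated for suicidal ideation, the primary question

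*Protocol article*

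**What the plan says.** The Sample Size section describes a calculation in G*Power and Excel, "applying the paired sample formula". It takes knowledge scores from a cited study: mean 16.88 before (95% CI 16.17 to 17.19) and 20.88 after (20.36 to 21.41). It converts the intervals to standard deviations, "yielding SD values of approximately 2.2 for preintervention and 1.2 for postintervention scores". It then sets "With a significance level (α) of .05, power (1–β) of 80" per cent and concludes with "an estimated effect size of 1.2, and a correlation coefficient of 0.5, the required sample size was determined to be 223 participants". The next sentence reads "Accounting for a 20% dropout rate [49], the final sample size was adjusted to 267 school-going adolescents" and names knowledge scores as what the power is for.

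Sidedness is not given there, but the abstract says outcomes are "analyzed using descriptive statistics, 2-tailed paired" t tests. Under Research Questions the primary question is "What is the effect of suicide prevention programs (RAAHI and safeTALK) in reducing suicidal ideation among school-going adolescents in GB". Suicide literacy and awareness are listed as secondary. The first null hypothesis concerns ideation risk at baseline and 8 weeks, and Data Analysis treats current ideation as a binary outcome in a population-averaged GEE. No other passage states a sample size or power.

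**The concern.** The paragraph gives all the inputs of a paired calculation, so its result can be checked. An effect size of 1.2 is very large for a paired test, and a requirement in the hundreds is not what it should produce. If 223 does not follow from the inputs, the only stated justification for 267 fails on its own figures.

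The choice of endpoint matters more. The paragraph covers a secondary outcome, so a reader of the trial report would have no planned detectable effect against which to judge a null result on suicidal ideation.

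**Working it through.** **Inputs.** From Sample Size: alpha 0.05, power 80%, effect size 1.2 (scale not stated), r = 0.5, SDs 2.2 and 1.2, means 16.88 and 20.88, result 223, dropout 20%, final 267. Two-sided testing is taken from the abstract.

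**1. Attempt to reproduce 223.** The SD of the paired difference is √(2.2² + 1.2² − 2 × 0.5 × 2.2 × 1.2) = √3.64 = 1.908. The number of pairs comes from the exact noncentral t, as in G*Power. The normal approximation is ((1.960 + 0.842)/dz)².

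| Reading of the inputs | dz | Pairs, exact | Pairs, normal |
|---|---|---|---|
| 1.2 is the standardised change | 1.2 | 8 | 6 |
| 1.2 is raw score points | 1.2/1.908 = 0.629 | 22 | 20 |
| Quoted mean difference | 4.00/1.908 = 2.10 | 5 | 2 |

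Other variants do not reach 223 either:
- One-sided testing gives 6, 18 and 4.
- 95% power, two-sided, gives 12, 35 and 6.
- Raw 1.2 with r = 0 gives 37.
- Two independent groups with raw 1.2 and SD 2.2 give 106 in total.

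In reverse, 223 pairs have 80% power for dz = 0.188, or 0.188 × 1.908 = 0.36 score points.

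**2. Dropout.** 223 × 1.2 = 267.6, which the article gives as 267. To keep 223 after 20% loss needs 223/0.8 = 278.75, so 279. With 267 enrolled, 267 × 0.8 = 213.6 remain. The loss that 267 can absorb is 1 − 223/267 = 16.5%. If 223 were the true requirement, power with 213 or 214 pairs would be about 78%.

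**3. Standard deviations (supporting note).** The interval widths are 17.19 − 16.17 = 1.02 and 21.41 − 20.36 = 1.05, so the half-widths are 0.51 and 0.525. With n = (1.96 × SD/half-width)², an SD of 2.2 implies about 71 observations and an SD of 1.2 about 20. The same respondents measured twice would give nearly equal SDs. The midpoint of the pre interval is 16.68, not the stated mean of 16.88.

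**4. What 213 completers can detect for ideation.** The article gives no effect, binary cutoff or within-person correlation for ideation, so these are assumptions shown as ranges. A McNemar calculation approximates the T1 to T3 contrast: n = [1.960√(p10 + p01) + 0.842√(p10 + p01 − Δ²)]²/Δ², with p11 = p1p2 + φ√(p1(1 − p1)p2(1 − p2)), p10 = p1 − p11 and p01 = p2 − p11.

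Worked case: p1 = 0.40, Δ = 0.109, φ = 0.3 gives p10 = 0.217 and p01 = 0.108, and so n = 213.

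| Baseline | φ = 0.7 | φ = 0.5 | φ = 0.3 | Relative fall |
|---|---|---|---|---|
| 40% | 7.2 points | 9.3 | 10.9 | 18 to 27% |
| 20% | 5.7 | 7.2 | 8.4 | 29 to 42% |
| 10% | 4.2 | 5.2 | 5.9 | 42 to 59% |

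These ignore clustering. The 40% row uses the adolescent ideation rate quoted in the Introduction, which comes without an instrument or recall period. The other two rows are illustrative.

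**The case against.** **Readers are not misled about the endpoint.** A reader might infer that the 80% power is presented as covering the primary question. The text does not support that, because the paragraph names knowledge scores openly. What stands is that ideation has no power statement.

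**The dropout slip is small.** A reader might also infer that ending below 223 leaves the trial short. For knowledge it does not: if the inputs are right, 213 pairs are far more than enough. Taken at face value the slip costs about 2 points of power.

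**The interval argument depends on an unseen source.** Near-equal widths could coexist with SDs of 2.2 and 1.2 if the numbers of respondents differed greatly before and after, and the off-centre mean could be one mistyped digit. That is implausible for paired data but not excluded, so it justifies a check against the source and no more.

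**An unstated clustering allowance might explain 223.** With four schools (about 56 to 67 students each) and a base of 22, it would need an intraclass correlation (ICC) of about 0.14 to 0.17; with a base of 8, 0.4 or more. The article mentions none.

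**The study is small and the number is fixed.** The article calls itself a feasibility study, and its abstract reports 267 already recruited. This limits the remedy to wording but does not make the calculation correct.

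**Conclusion.** The point holds and should be corrected. The stated inputs require 5, 8 or 22 pairs depending on how 1.2 is read, so 223 is at least ten times what they support. This needs no assumption beyond two-sided testing, and one-sided testing does not rescue it. The dropout error is certain but minor: 267 where 279 was needed, or cover for 16.5% loss where 20% was claimed.

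The most consequential part is that the primary outcome has no power basis. It would go too far to say that 267 is too few for ideation. The article states no target effect, and the detectable fall runs from about 4 to 11 points depending on baseline and correlation, before clustering. The sample may or may not suffice, and the article gives no means of telling which.

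**What to change.** Keep 267 and rewrite the Sample Size paragraph:

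- Check the cited means and intervals against the source. Remove or correct the SDs and the 1.2 effect size so that the stated inputs give the stated number.
- State that 267 leaves about 213 completers at 20% loss, or covers 16.5% loss if 223 are needed.
- Say that knowledge scores are amply powered.
- Add the detectable T1 to T3 change in suicidal ideation for the planned binary GEE, naming the cutoff, baseline and within-person correlation assumed. With 213 completers, 80% power and correlation 0.7 to 0.3, this is an absolute fall of about 7 to 11 points at a 40% baseline, 6 to 8 at 20% and 4 to 6 at 10%, before clustering. Show any design effect together with its assumed ICC. A standardised change of 0.19 should not be quoted for ideation, because the planned analysis is binary.

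The cost is one reworded paragraph and less favourable stated figures, with no extra participants and no change in conduct.

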### Recruitment of Participants

#### Step 1

Participants will be recruited from 4 private schools under the Aga Khan Education Service network using consecutive sampling. Approval will be obtained from the school principals, followed by coordination with the administration to arrange a designated space for study activities.

#### Step 2

A recruitment flyer will be distributed to students in grades 9 and 10. Interested students will be instructed to contact their parents to obtain initial verbal consent before participation.

#### Step 3

Parents will be provided with study details in a private setting. The researcher will explain the study’s purpose, procedures, and expectations, addressing any questions. Written informed consent will be obtained for eligibility screening, intervention participation, and pre- and posttest assessments. To ensure transparency, parents will also receive a copy of the consent form for further review.

#### Step 4

Eligible students will be identified based on predefined criteria. Those who meet all eligibility requirements will be enrolled in the study.

To mitigate low participation rates, multiple outreach efforts, including follow-up meetings, will be conducted. In cases where logistical constraints arise, such as scheduling conflicts or space limitations, alternative arrangements (eg, rescheduling sessions or using available classrooms) will be made to facilitate smooth study implementation.

### Procedure

#### Intervention 1: RAAHI

RAAHI is a suicide literacy module that is specially designed to provide individuals with essential knowledge and skills by equipping them with tools to navigate the complexities of mental health and suicide prevention. This module aims to empower people to recognize signs of suicidal ideation, engage in empathetic communication through open discussion, combat stigma, and connect individuals in crisis with appropriate support and resources. The duration of the module will be 3 hours. Hence, RAAHI seeks to create a world where suicide literacy is widespread, compassion is the key to preventing tragedy, and no one feels isolated in their struggle, thereby contributing to a more empathetic and supportive future (Table 1).

#### Intervention 2: safeTALK

The safeTALK program is an educational initiative designed for suicide prevention among adolescents, consisting of a 4-hour workshop that incorporates presentations, videos, discussions, and questions. The workshop is designed according to the standard practices of safeTALK to assist participants in (1) identifying warning signs of suicide; (2) avoiding frequent impulses to overlook, dismiss, or avoid discussions about suicide; (3) recognizing and responding to situations where suicidal thoughts may be present by applying fundamental TALK steps; and (4) connecting individuals contemplating suicide with first aid assistance and additional community resources [2]. The skill training program concentrates on bolstering adolescents’ understanding of activities that promote mental well-being, fostering resilience, honing distress management abilities, and enhancing their capacity to identify early signs of suicidal ideation or behavior both within themselves and among others. The program also equips participants with strategies for suicide crisis intervention.

The intervention involves the components mentioned subsequently.

### Phase 2: Testing the Effectiveness of the Suicide Prevention Program

#### Pretest Phase

Students willing to participate will be asked to provide their consent by signing a form or paper before starting the pen-and-paper pretraining survey. Students will be explicitly informed that participation is entirely voluntary, and their decision to participate or not to participate will not affect their training in any way. First, the psychologist and the researcher will conduct a risk assessment of the students for any previous history or current complaints of suicidal ideation and behavior. A 40- to 60-minute window will be allocated before the training commences to enable participants to complete the pretest survey. In addition, the level of suicide literacy will also be evaluated through validated and self-report questionnaires. Along with this, students’ level of confidence and willingness to discuss suicidal ideation and attitudes toward seeking help from others, adopting coping abilities, and self-efficacy level will also be assessed. Following the pretest phase, the students will enter the intervention phase.

#### Intervention

The intervention phase consists of 2 workshops in which the students will be required to participate. The first workshop consists of 2 hours of RAAHI intervention which will provide them with general knowledge about suicide, risk factors, consequences, and preventive strategies; this will help participants improve their suicide literacy. Moreover, a booklet comprising different activities will also be provided to participants during the training. In addition, the second session will introduce the 4-hour safeTALK program, which seeks to increase people’s self-awareness and help-seeking behavior while reducing suicidal ideation. This is a culturally relevant program as it applies basic TALK steps and connects the person with suicidal thoughts with suicide first aid help and further community resources. Moreover, a pocket card containing the “suicide alert steps” will also be provided to the participants at the end of the training. In this study, the safeTALK workshops will be delivered to adolescents, approximately 30 students at a time. The researcher, along with a psychologist, will administer this training with the help of translated videos and material in Urdu, which is culturally appropriate and has been modified and adapted from LivingWorks.

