### Data Collection

The principal investigator has received safeTALK training from LivingWorks and will train data collectors for the data collection process. The training includes presentations, videos, discussions, questions, and role-play. All participants will receive identical training at no expense, with no alterations in the delivery or content. Demographic information will be solely collected from participants who provide consent and agree to complete both pre- and posttraining surveys; however, the analysis will be restricted to data furnished by those who complete the surveys based on per-protocol analysis [73]. To promote data quality, study personnel will be trained in the administration of these instruments, and procedures for double data entry, verification, and management will be implemented to ensure accuracy and completeness. Data collection forms will be securely stored, with access limited to authorized personnel to maintain confidentiality [74]. Strategies to promote participant retention and complete follow-up will include clear communication about the study’s importance and duration during the consent process, maintaining regular contact with participants and ensuring the study procedures are convenient and acceptable. For participants who discontinue or deviate from intervention protocols, efforts will be made to collect available outcome data to allow for intention-to-treat analysis, where feasible.

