### Time Frame for Data Collection

Each participant will receive a short questionnaire at 3 points in time: pretest baseline data (T1), immediately after the intervention (T2), and 8 weeks after the intervention (T3). This self-filled questionnaire will collect data on suicidal ideation, level of suicide literacy, level of confidence, and openness to disclose suicidal ideas to others. The researcher will be responsible for checking for and verifying any missing data with participants, which will help to identify and correct errors in the datasets.

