### Data Monitoring and Management

Data monitoring and management for this study, coordinated by the School of Nursing and Midwifery at the Aga Khan University, with strategic guidance from a steering committee, involves several key roles and processes. Trained psychologists will collect data, while the primary author will oversee data management (entry validation, cleaning, and secure storage) and monitor participant safety during data collection using safeTALK training, with protocols for immediate counselor referrals if distress occurs. A dedicated, separate data analyst will conduct statistical analyses. An independent data monitoring committee, composed of external experts, including clinicians and a biostatistician operating under a charter, will periodically review trial data for safety, efficacy, and overall conduct, managing interim analyses with predefined stopping guidelines and restricted access to results. Comprehensive procedures are in place for managing and reporting adverse events, with investigators responsible for the timely reporting of serious events. Finally, independent personnel will conduct periodic audits, detailed in a separate plan, to ensure trial quality and compliance.

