### Potential Risk to Participants

This study has minimal potential risks for the participants. While obtaining informed consent from the parents and assent from the participants, it will be made clear that information regarding those considered susceptible, based on their scores, will be shared with their parents, and they will be referred for further assessment after the parents’ consent. However, the status of the participants will be kept confidential from the school authorities. The study will involve psychologists who will conduct the interview along with the principal investigator; hence, they will be able to screen the potential participants.

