### Strengths and Limitations

Because there is no standard intervention available for suicide prevention for adolescents in the Pakistani context, this research will assist in upscaling suicide prevention interventions tailored to the cultural and social context of GB among school-going adolescents in Pakistan. This study aims to bridge this gap by evaluating the effectiveness of suicide prevention programs specifically designed for Pakistani adolescents, thereby providing crucial data to inform national mental health strategies and policies. This study’s strong pre- and postintervention design enabled a clear evaluation of the program’s immediate effect on participants’ mental health. The use of established measurement instruments bolsters the dependability of our results.

However, due to time, budget, and logistical constraints, this feasibility study will only be conducted in 4 schools in GB, Pakistan, limiting potentially diverse implementation experiences and outcomes in rural or public-school settings. This may restrict the generalizability of the study findings. Moreover, using a quasi-experimental design without an appropriate control group can potentially undermine the internal validity of the study. Third, this study’s sample was limited to school-going adolescents, potentially restricting the generalizability of findings to out-of-school adolescents or other high-risk groups. In addition, the absence of a long-term follow-up limits our ability to determine the sustained impact of these interventions. However, reliance on self-reported data raises the possibility of response biases, particularly social desirability, which is significant given the prevailing mental health stigma in this area. Furthermore, while we acknowledge the potential influence of factors such as socioeconomic status, family support, and preexisting mental health issues, these were not fully controlled in our analysis. Future research should strive to include a broader range of variables to strengthen the study’s conclusions. Finally, it is important to note that the results of this investigation are specific to the studied context and may not be readily applicable to different cultural or geographic populations.

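### Workshop delivery is not kept apart from outcome collection: the researcher who co-delivers also queries missing answers on the ideation questionnaire, in a single-group design that cannot remove a reporting shift

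*Protocol article*

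**What the plan says.** **Delivery.** Under Intervention (Phase 2): "The researcher, along with a psychologist, will administer this training with the help of translated videos and material in Urdu".

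**Queries on incomplete forms.** Under Time Frame for Data Collection: "The researcher will be responsible for checking for and verifying any missing data with participants". The same section fixes the mode at baseline (T1), straight after the workshops (T2) and 8 weeks later (T3): "This self-filled questionnaire will collect data on suicidal ideation, level of suicide literacy, level of confidence".

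**Collection.** Under Data Monitoring and Management: "Trained psychologists will collect data, while the primary author will oversee data management". The section on ancillary care and referral also has psychologists collecting the data. Under Data Collection, the principal investigator "will train data collectors for the data collection process".

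**A face-to-face contact.** Under Pretest Phase, the psychologist and the researcher first carry out a risk assessment for past or current ideation, and the survey there is on paper. Under Potential Risk to Participants: "The study will involve psychologists who will conduct the interview along with the principal investigator". That sentence goes on to link the interview to screening.

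**Design and admitted limits.** Study Design rules out a control group. Null Hypotheses compares ideation at baseline with 8 weeks. Strengths and Limitations concedes that "reliance on self-reported data raises the possibility of response biases, particularly social desirability", and describes this as significant given local stigma.

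**The concern.** The researcher teaches a group about suicide and then returns to individual students in that group over blanks on a questionnaire that asks about their own suicidal thoughts. A student who knows that the trainer handles the form may answer, or complete an omitted item, with the trainer in mind. Students cannot be blinded to the programme, but the trainer can be kept away from the form.

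In a controlled trial with the same collectors in both arms, some of this would cancel. Here the primary answer is a within-person change from T1 to T3, and no comparison group subtracts a reporting shift. The adjustments and sensitivity analyses promised under Study Design are aimed at biases such as maturation and historical events. Trainer-directed reporting is not named among them, and a later model could not recover it from these data. The article admits social desirability in general but gives no procedure to limit the part that comes from deliverers handling outcome forms.

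A second, smaller problem is that the mode of the primary measure is left open to doubt. The questionnaire is self-filled in one section, while another refers to an interview, and the article does not say that the interview plays no part in the outcome score.

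**Working it through.** **1. Roles side by side**

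| Task | Role named | Section |
|---|---|---|
| Delivers training | researcher and a psychologist | Intervention |
| Pretest risk assessment | psychologist and researcher | Pretest Phase |
| Collects data | trained psychologists | Data Monitoring and Management; Ancillary and Posttrial Care |
| Queries missing answers with students | researcher | Time Frame for Data Collection |
| Analyses data | separate analyst | Data Monitoring and Management |

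The overlap is explicit for the researcher. For psychologists it is an overlap of role: the article does not say whether the co-delivering psychologist also collects from the same group. The separate analyst acts only after the answers have been given. Coded forms do not remove the problem, because querying a blank means linking a form to a student.

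**2. Mode**

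Time Frame for Data Collection says self-filled at all three time points. Data Collection Tools puts the Modified Scale for Suicidal Ideation (MSSI) in the same first section of the survey as the eligibility questions. Potential Risk to Participants refers to an interview tied to screening, and says that students are identified as susceptible by their scores. Most naturally this is the pretest risk assessment, but the sections do not say so.

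**3. Illustration of size**

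The plan gives no figure on this point to reproduce. Inputs:
- n = 223, the required number before the dropout allowance (Sample Size), taken here as completers.
- π = 0.40, baseline ideation. This is the Pakistani adolescent figure in the Background, not an expected rate in these schools.
- s = 0.05, the share of all students who truly switch in each direction, so there is no true net change (assumed).
- c, the share of students with ideation at T3 who do not report it (assumed).

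Cell probabilities:
- reported at T1 but not at T3: p10 = s + (π − s)c
- reported at T3 but not at T1: p01 = s(1 − c)
- spurious net fall: p10 − p01 = πc

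For c = 0.10: p10 = 0.05 + 0.35 × 0.10 = 0.085 and p01 = 0.045. The net fall is 0.04, so reported ideation goes from 40% to 36%. Expected discordant pairs are 223 × 0.085 = 19.0 against 223 × 0.045 = 10.0.

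For c = 0.20: p10 = 0.12 and p01 = 0.04. The net fall is 0.08, and expected pairs are 26.8 against 8.9.

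The probability that a two-sided exact McNemar test gives p < 0.05 (a stand-in for the planned generalized estimating equation) is:

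| Baseline ideation | c = 0 | c = 10% | c = 15% | c = 20% | c = 25% |
|---|---|---|---|---|---|
| 40% | 3% | 31% | 59% | 83% | 95% |
| 20% | 3% | 10% | 20% | 33% | 49% |
| 10% | 3% | 5% | 7% | 11% | 16% |

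At 40% baseline and c = 20%, changing s from 2% to 8% moves the result from 95% to 72%. At c = 10% it moves from 51% to 24%.

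**The case against.** **The overlap may be smaller than it looks.** One psychologist delivers, several collect, and trained data collectors are mentioned. A reader might infer that the same people deliver and collect throughout. The article does not say that; only the researcher's double role is explicit. The researcher's stated task also concerns missing answers, so it does not show the trainer questioning answers already given. Both limits stand.

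**The MSSI is not shown to be taken by interview.** A reader might infer that the mode is both self-filled and interview, or that it changes between time points. No section says either. What stands is that the sections need to be reconciled.

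**Students meet these roles at T1.** The pretest risk assessment means the baseline is not free of contact with them. That is true, and it weakens a sharp contrast between T1 and T3. The teaching relationship still begins after T1.

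**The direction is not fixed.** The programme aims to reduce stigma and encourage open discussion, which could raise reported ideation. This stands.

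**The illustration does not isolate the trainer.** It counts under-reporting from any cause, including the sharing of susceptible students' information with parents, which this fix leaves untouched. This also stands. A tempting stronger calculation assumes no switching in the other direction: 9 of 89 positives (40% of 223) fall silent, and exact p = 2 × 0.5⁹ = 0.004. That is the most favourable case for significance and should not be quoted as typical.

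**A staff rota is operational detail that an article may omit.** In part. But the article does state who does what, and the roles it states overlap.

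**Conclusion.** The point holds in a limited form. One role, the researcher, is assigned both delivery and the follow-up of missing answers on the questionnaire that contains the primary outcome. Psychologists as a group appear on both sides, and no separation is stated. Because the design is single-group and pre-post, whatever reporting shift this causes becomes part of the estimated effect. It adds to the admitted social desirability, and it is the part that conduct can reduce.

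Its size cannot be known from the article. The 31% to 83% range rests on 40% baseline ideation, 223 completers, no true change, 5% switching each way and 10% to 20% concealment. The same concealment gives 10% to 33% at 20% prevalence and 5% to 11% at 10% prevalence. A reader might infer that the bias certainly favours benefit; less reported ideation is the more likely direction, but the documents do not establish it. This should be changed, but it does not by itself invalidate the study.

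**What to change.** 1. For each workshop group, have outcome forms handed out, collected and queried for missing items at T1, T2 and T3 by an existing data collector or psychologist who did not deliver that group's workshop. At about 30 students per workshop, 267 students make roughly nine groups (267 / 30 = 8.9), so rotation looks feasible.
2. For groups already past T1, record who handled the forms at each time point. Changing the handler between T1 and T3 would itself add a difference, and the article's dates leave it unclear how far collection has gone.
3. Reconcile Pretest Phase, Time Frame for Data Collection and Potential Risk to Participants. State that the MSSI outcome is self-completed at all three time points, and that the risk-assessment interview is a separate safety step that never supplies or changes an outcome score.
4. In Strengths and Limitations, say that a fall in reported ideation cannot be separated from a change in reporting.

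The safety review of scores stays as the protocol provides. The cost is some protocol wording, a staff rota and less scheduling flexibility.
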